#### Concurrent sexual partners

Concurrency among men partnered in the last 12 months is assessed using the following question: ‘Have you had a sexual relationship with any other woman in the last 12 months, while being with your wife/partner/most recent partner?’ Polygamous men will be excluded from the denominator as the intervention is not expected to impact on polygamous marriages over this relatively short follow-up period.

Questions on sexual behaviour are asked in accordance with widely accepted guidelines [57]. Confidentiality is stressed throughout the interview process, and as already stated interviews are conducted in private by a trained interviewer of the same sex as the respondent.

### Quantitative data collection and management

Survey tools will be used to collect data on outcome measures and on potential confounders, pathway variables and contextual variables. All completed questionnaires will be checked by field supervisors upon completion, and where problems are identified with a questionnaire it will be returned to the interviewer for corrections or for information to be completed. Once a supervisor has checked a questionnaire and cleared it as complete and satisfactory, it is sent to the Raising Voices offices. There it will be re-checked by a fieldwork coordinator or data manager. Data will be double-entered and stored in purpose built Microsoft Access databases. Where discrepancies are noted between twin-entries, reference to the original questionnaire will be made to determine the correct entry. Additional rigorous data cleaning procedures will be applied which will also entail reference to source data. Data backups will be made weekly and stored, password-protected, on a secure central drive at Raising Voices. All electronic data are anonymous. Questionnaires will be stored in locked filing cabinets in a locked office.

### Sample size

Sample size for a community randomised trial must be defined at two main levels, the level of randomisation (number of communities randomised) and the level of data collection (number of individuals surveyed in each community). In this study, a decision also had to be reached as to how many CAs to sample around within each site. For the SASA! study, sample sizes at each of these levels were decided upon based on a combination of pragmatic and theoretical considerations. The aim was to conduct the highest powered study deemed feasible given resource and staffing constraints surrounding intervention implementation and data collection. Based on these considerations, at baseline we decided on a target sample size of 200 people per site (1600 in total) for the community survey. Broken down to the different sampling levels, we aimed to complete surveys around 8 CAs in each site, and with 25 eligible people around each CA. The sample was designed to include an equal number of male and female respondents in each site.

Allowing for failure to contact respondents, refusals to participate, and households without any eligible members, we over-sampled by 40%. This figure was based on estimates of the age- and sex-distribution of Kampala’s population derived from the 2006 Uganda DHS, and male and female response rates for the same survey. It was then revised upwards to allow for the fact that recent arrivals to the parish would be ineligible to participate. Therefore, the final sample size for households to be visited was 2,240 in total (35 households around each CA).

With a final sample size of four communities and eight hundred respondents per arm (100 men and 100 women per site), we calculated the precision with which we would be able to estimate a range of effect sizes for the outcomes hypothesised to be most distal to the intervention and hardest to change, therefore, the ones for which the magnitude of change was expected to be smallest (physical and sexual IPV; and concurrent partnerships). Precision estimates, in the form of a 95% CI (the range of likely values for the true effect), are presented in Table 1. In a community randomised trial, the precision of an estimate for a given outcome and effect size is based on the number of study communities, the number of individuals surveyed in each community, and the size of the coefficient of variation (k) for the outcome of interest [58]. There are few reported data on coefficients of variation, and we therefore present precision estimates for each outcome assuming a range of different values of k. Based on other studies, we expected the value of k to be highest for past year experience of IPV (approximately 0.4) [25] which has been shown to cluster by community.

**Table 1 T1:** Precision estimates for effect sizes given varied assumptions about control-arm prevalence and between-community variation

**Outcome**	**Estimated final sample size per site (with 4 intervention and 4 control sites in total)**	**Estimated prevalence of outcome measure**		**Effect estimate**	**Estimate of precision of percentage risk difference (95% CI)***			
		**Control arm (%)**	**Intervention arm (%)**	**Risk difference (%)**	**k = 0.1**	**k = 0.2**	**k = 0.3**	**k = 0.4**
Past year experience of physical IPV (women partnered in past year)	75 (based on 100 respondents per site, 80% having partner in past year and 5% non-response to violence questions)	30.0	22.5	7.5	−2.4, 17.4^a^	−5.2, 20.2 ^a^	−8.8, 23.8 ^a^	−12.9, 27.9 ^a^
		30.0	15.0	15.0	5.8, 24.2	3.4, 26.6	0.2, 29.8	−3.4, 33.4 ^a^
		20.0	15.0	5.0	−3.2, 13.2 ^a^	−4.7, 14.7 ^a^	−6.9, 16. 9 ^a^	−9.4, 19.4 ^a^
		20.0	10.0	10.0	2.4, 17.6	1.1, 18.9	−0.8, 20.8 ^a^	−3.0, 23.0 ^a^
Past year experience of sexual IPV (women partnered in past year)	75 (based on 100 respondents per site, 80% having partner in past year and 5% non-response to violence questions)	15.0	11.0	4.0	−3.1, 11.1 ^a^	−4.1, 12.1 ^a^	−5.6, 13.6 ^a^	−7.3, 15.3 ^a^
		15.0	7.5	7.5	0.9, 14.1	0.0, 15.0	−1.3, 16.3 ^a^	−2.8, 17.8 ^a^
		10.0	7.5	2.5	−3.4, 8.4 ^a^	−3.9, 8.9 ^a^	−4.8, 9.8 ^a^	−5.8, 10.8 ^a^
		10.0	5.0	5.0	−0.4, 10.4 ^a^	−0.9, 10.9 ^a^	−1.7, 11.7 ^a^	−2.6, 12.6 ^a^
Concurrent sexual partners (among non-polygamous men partnered in the past year)	75 (based on 100 respondents per site, 80% having partner in past year and 5% non-response to sexual behaviour questions)	50.0	37.5	12.5	0.0, 25.0	−5.7, 30.7 ^a^	−12.5, 37.5 ^a^	−19.7, 44.7 ^a^
		50.0	25.0	25.0	13.4, 36.6	8.4, 41.6	2.4, 47.6	−3.9, 53.9 ^a^
		40.0	30.0	10.0	−1.3, 21.3 ^a^	−5.5, 25.5 ^a^	−10.7, 30.7 ^a^	−16.3, 36.3 ^a^
		40.0	20.0	20.0	9.5, 30.5	5.9, 34.1	1.3, 38.7	−3.7, 43.7 ^a^

*Based on calculations provided by Hayes and Bennet (1999) [58].

^a^No statistically significant difference between intervention and control groups.

*IPV*, intimate partner violence.

Using baseline data from the SASA! study, we now have a better indication of the effect sizes we will be able to detect. Baseline prevalence of past year physical IPV was 23%. Variation between communities was lower than would be expected by chance assuming a binomial model, but to allow for random error in our estimate of the coefficient of variation within matched pairs (k_m_), we conservatively assume a k_m_ value of 0.1. We should thus be able to detect a 39% or greater reduction in relative risk of past year physical IPV. Data on baseline prevalence and k_m_ for the other health related outcomes show that we should be able to detect a 58% or greater reduction in relative risk of past year sexual IPV, and a 33% or greater reduction in relative risk of past year concurrent partnering among men (Table 2).

**Table 2 T2:** Minimum detectable risk differences for outcomes based on baseline prevalence and coefficients of variation

**Outcome**	**Baseline prevalence**	**Average number of individuals per cluster with outcome data**	**K**_**m**_	**Minimum detectable risk difference**	**Minimum detectable reduction in relative risk**
Past year physical violence (women)	23%	72	<0.1	9%	39%
Past year sexual violence (women)	12%	72	0.16	7%	58%
Past year concurrent partners (men)	45%	83	0.17	15%	33%

At the time of writing the budget for the follow-up study had increased and we have decided to increase our sample size within sites. This will give us more power to perform secondary sub-group analyses which will allow us to better understand variations in intervention impact between different sub-groups in the communities, thereby adding to our understanding of the transferability of study results. The follow-up survey will thus take place around all 96 CAs, with a target sample size of 25 eligible people around each CA and total target sample size of 2,400 individuals. With oversampling, the total number of households to be visited is '3360' in total (35 households around each CA).

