### Evaluation design

The study employs a matched cluster randomised design, with randomisation carried out within matched community pairs. As described previously, the comparison groups comprise four intervention communities (receiving the full intervention) and four control communities (receiving only Division level elements of the intervention) (Figure 3). Quantitative data collection will occur before (baseline) and four years after (follow-up) implementation of the intervention. It is important to note that a four-year follow-up period does not equate to four years of programming - barriers to programme activity including political disturbances and the suspension of activities during political election campaigns, mean that the duration of SASA! programming will have been approximately 2.8 years by the time of the follow-up survey. At each time-point, data will be collected from a cross-sectional sample of community members targeted by the intervention, and from community activists.

The primary analysis will compare intervention and control communities at follow-up. This protocol focuses on the CRT element of the evaluation that will assess the impact of the intervention on the outcomes identified in the first trial objective. However, in addition to this, monitoring and evaluation data will be collected throughout the duration of the study, including through repeated rapid assessment surveys of community members. These data will be used to document, among other things, how the intervention is implemented, its evolution in different communities, CA retention/turnover, the people it reaches, diffusion of activities into control communities, barriers to intervention delivery, and other relevant activities and policy changes that occur over the time period of the study.

A complementary ongoing programme of qualitative data collection will also allow more in-depth understanding of the implementation and processes of the intervention, including community perceptions of it, the forms of behaviour change being promoted, and the ways in which change is occurring at different levels and among different groups.

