### Data analysis

#### Primary analysis

The primary analysis will be a cluster-level analysis of the community survey data using a two-stage approach similar to that used in several recent studies evaluating community-based HIV and violence prevention interventions in Africa [25,33]. We will use an unpaired analysis in order to maximise statistical power given the small number of sites randomised [59], and will follow the basic principles for the analysis of cluster randomised trials as set out by Donner and Klar [60].

The analysis will be done on an intention to treat (ITT) basis, whereby data on all respondents are included whether or not they report any contact with the intervention.

Site-level past year prevalence of the outcome will be generated. The geometric mean of site-level prevalences will be calculated for intervention and control villages respectively, and the ratio of these two figures (geometric mean prevalence ratio) used to give us an estimate of crude intervention effect. An unpaired *t*-test will be used to compare the logarithms of the prevalence figures and assess the statistical significance of the difference in outcomes between intervention and control sites.

The generation of adjusted prevalence ratios for each of the outcome measures involves two stages. First an individual-level binary logistic regression model, in which the dependent variable is the binary outcome of interest, will be fitted to data from control villages. Independent variables will include measures of potential confounders (age, sex and baseline EA-level prevalence of the outcome measure of interest). This model will be used to predict the number of people in each site (intervention and control sites) that would be expected to experience the outcome at follow-up in the absence of the intervention. For each site, the ratio of observed to expected (O/E) numbers with the outcome will then be calculated. A geometric mean of these site-level summary measures will be calculated for intervention and control sites respectively, and a ratio of these means used to generate a point estimate of the adjusted intervention effect. As with the crude estimates, an unpaired t-test will be used to assess the statistical significance of this comparison and construct a 95% CI around the adjusted prevalence ratio.

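### Table 2 puts the within-pair variation k_m into an unpaired 6-df calculation, so its detectable differences are best-case values that may be too small for the planned analysis

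*Protocol article*

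**What the plan says.** The Evaluation design section states: "The study employs a matched cluster randomised design, with randomisation carried out within matched community pairs". There are four pairs. The Primary analysis section then sets the pairing aside: "We will use an unpaired analysis in order to maximise statistical power given the small number of sites randomised". For the crude effect, this unpaired "test will be used to compare the logarithms of the prevalence figures"; the adjusted effect is also tested with an unpaired t-test, on observed-to-expected ratios.

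The Sample size section gives two sets of figures. Table 1 uses k, the between-community coefficient of variation, over 0.1 to 0.4, with about 0.4 expected for IPV from other studies. Table 2 updates this from the baseline survey but switches to k_m. For physical IPV the text reports that variation between communities was below what a binomial model predicts, and continues: "to allow for random error in our estimate of the coefficient of variation within matched pairs (k_m_), we conservatively assume a k_m_ value of 0.1". The other two rows use k_m of 0.16 (sexual IPV) and 0.17 (concurrency), and no allowance for random error is described for them. The stated minimum detectable differences are 9, 7 and 15 percentage points, or 39%, 58% and 33% in relative terms. No unpaired baseline k is given.

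**The concern.** Matching helps precision only if the analysis removes the between-pair component. A paired analysis does so and pays with degrees of freedom: 3 for four pairs. An unpaired analysis keeps 6 df but leaves the between-pair component in its error. With k² = k_m² + between-pair variance (relative scale), the input for the planned test is k. Taking k_m together with 6 df combines the smaller variance of one analysis with the smaller multiplier of the other, and the result describes neither. The protocol chooses the unpaired analysis for its power, so the variance cost of that choice should appear in its detectable effects.

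The second issue is the word *conservatively*. Raising k_m to 0.1 is the only stated protection against an imprecise estimate, and the estimate comes from eight sites.

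At stake are the protocol's stated detectable effects. They tell readers how to weigh a null result on violence or concurrency.

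**Working it through.** **Inputs.** From the Sample size section: c = 4 sites per arm. Table 2 baseline prevalence p0, respondents per site n, and k_m: physical IPV 23%, 72, 0.1 (printed as <0.1); sexual IPV 12%, 72, 0.16; concurrency 45%, 83, 0.17. The follow-up target is 2,400 against 1,600, so 1.5 times n: 108, 108 and 124.5.

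**Formula** (the variance that reproduces Table 1): SE² = [p0(1−p0)/n + p1(1−p1)/n + k²(p0² + p1²)]/4, and the detectable difference d = p0 − p1 solves d = t × SE. Multipliers: 2.447 (6 df) or 3.182 (3 df).

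**Check on Table 1.** First row, 30% v 22.5%, n = 75, k = 0.1: 0.00280 + 0.00233 + 0.00141 = 0.00653; SE = √(0.00653/4) = 0.0404; ×2.447 gives ±9.9 points, so −2.4 to 17.4 as printed. The 6-df multiplier reproduces all 48 half-widths to within 0.1 point. The normal multiplier misses by up to 6.5 points and 3 df by up to 9.6.

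**Reproducing Table 2** with k = k_m:

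| Outcome | Stated | 6 df | 3 df (consistent with k_m) |
|---|---|---|---|
| Physical IPV | 9 | 8.6 | 10.8 |
| Sexual IPV | 7 | 6.3 | 7.9 |
| Concurrency | 15 | 14.5 | 18.3 |

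The 6-df values rounded up to whole points are exactly 9, 7 and 15, and 9/23, 7/12 and 15/45 give 39%, 58% and 33%. The normal multiplier gives 8, 6 and 12; 3 df gives 11, 8 and 19. So Table 2 is k_m in the unpaired calculation.

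**Largest unpaired k at which the stated difference still has a 95% CI excluding zero (6 df):**

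| Outcome | k_m used | at Table 2 n | at 1.5 × n |
|---|---|---|---|
| Physical IPV | 0.1 | 0.13 | 0.19 |
| Sexual IPV | 0.16 | 0.26 | 0.33 |
| Concurrency | 0.17 | 0.18 | 0.20 |

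Concurrency has almost no margin. At p1 = 30% the three terms are 0.00298 + 0.00253 + 0.00845, so the k term is already 61% of the total (0.00845/0.01397), and adding respondents does little.

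**Detectable difference in points by assumed unpaired k (6 df), Table 2 n / 1.5 × n:**

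| Outcome | k = k_m | 0.2 | 0.3 | 0.4 |
|---|---|---|---|---|
| Physical IPV | 8.6 / 7.4 | 10.1 / 9.2 | 12.0 / 11.3 | 14.1 / 13.6 |
| Sexual IPV | 6.3 / 5.5 | 6.6 / 5.8 | 7.3 / 6.7 | 8.2 / 7.7 |
| Concurrency | 14.5 / 13.6 | 15.9 / 15.2 | 20.7 / 20.2 | 25.5 / 25.1 |

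These k values are assumptions; they are the range of Table 1.

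**How much does sub-binomial variation say about physical IPV?** The binomial part of the squared coefficient of variation is 0.77/(0.23 × 72) = 0.0465. If true k were 0.2, the expected value would be 0.0465 + 0.04 = 0.0865, a ratio of 0.538. The chance that the observed value still falls below binomial is P(χ²₄ < 4 × 0.538) = 29% if variation was measured within the four pairs, or P(χ²₇ < 7 × 0.538) = 19% if measured across all eight sites. So the baseline result is quite compatible with k = 0.2, which requires 10.1 points (44%) at n = 72 or 9.2 points (40%) at n = 108.

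**The case against.** A reader might infer that the detectable effects are definitely understated, and that the physical IPV figure is really nearer 61%, the value at k = 0.4. The documents do not support that.

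- The unpaired baseline k is not reported. Matching used staff's qualitative judgement of density and population mobility, which may explain little of these outcomes; k would then equal k_m and the 6-df figures would stand.
- For physical IPV the text describes variation *between communities* as already sub-binomial. The point estimate is then zero, 0.1 lies above it, and the k/k_m swap is not shown to change that row.
- The 0.4 came from other studies, and the protocol says its baseline data give a better indication. With a true k of 0.4, sub-binomial variation would be seen only about 8% (4 df) or 2% (7 df) of the time. The observed variance is not given, so no firm upper bound on k can be computed.
- The follow-up sample is 1.5 times larger. If k does equal k_m, Table 2 is pessimistic for that survey.
- Adjustment for baseline EA-level prevalence may remove some between-pair variation.
- Table 1 already shows sensitivity to k. The protocol admits low precision, puts direction and coherence ahead of significance, and set the number of sites by feasibility.

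All of this limits the size of the problem. It does not make Table 2 match the planned test. Table 2 claims no credit for adjustment and does not use the follow-up sample, and Table 1 does not correct the specific figures that the text says the trial can detect.

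**Conclusion.** The mismatch stands: Table 2 joins a paired variance to an unpaired multiplier. For the k_m entered and the tabled cluster sizes, 9, 7 and 15 points are the best case for an unpaired analysis and can be too small; a consistent paired analysis needs 10.8, 7.9 and 18.3. The size of any understatement cannot be derived and may be zero.

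The exposure differs by outcome. Concurrency is the weakest row, because a rise in k from 0.17 to just above 0.18 (0.20 at follow-up size) defeats the stated 15 points. Sexual IPV has room, up to k of about 0.26 (0.33). For physical IPV the problem is the thin allowance: *conservatively* claims more than eight sites can support. For the other two rows no allowance is described.

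This rests on the risk-difference formula that reproduces Tables 1 and 2 (the planned test is on log prevalences), on k being at least k_m, and on a chi-squared approximation for the sub-binomial probabilities.

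**What to change.** Recompute Table 2 with the unpaired within-arm k estimated from the eight baseline sites, reported with its uncertainty, using 6 df and the planned follow-up cluster sizes. Show each outcome over a range of k, as Table 1 does. If k_m is kept instead, use 3 df and say that the figures belong to a paired analysis, which is not the one planned. Replace *conservatively* with a plain statement of how uncertain k is, and apply the same treatment to sexual IPV and concurrency.

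The cost is a recalculation from data already held. Design, sample and primary test are untouched. Depending on the unpaired k, the revised figures may be less favourable than those printed or, with the larger follow-up sample, somewhat better.

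### Table 2's minimum detectable reductions (39%, 58%, 33%) carry no stated power and best match significance thresholds; at the table's own inputs, power for effects of that size is about 57–64%

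*Protocol article*

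**What the plan says.** The Sample size section first presents a precision exercise: "With a final sample size of four communities and eight hundred respondents per arm (100 men and 100 women per site") is the stated basis, and "Precision estimates, in the form of a 95% CI (the range of likely values for the true effect), are presented in Table 1". Table 1 flags each interval by whether it shows a significant difference.

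The section then moves from precision to detection. With the baseline survey in hand, "we now have a better indication of the effect sizes we will be able to detect". For physical IPV, where between-site variation at baseline was below binomial expectation, "we conservatively assume a k_m_ value of 0.1". The conclusion drawn is "We should thus be able to detect a 39% or greater reduction in relative risk of past year physical IPV", and for the other two outcomes a "58% or greater reduction in relative risk of past year sexual IPV, and a 33% or greater reduction in relative risk" of concurrent partnering. Table 2 prints these as minimum detectable values:

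- physical IPV: 9 points (39%)
- sexual IPV: 7 points (58%)
- concurrency: 15 points (33%)

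The average cluster sizes are 72, 72 and 83. No power is given for any of them.

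The next paragraph enlarges the follow-up survey to a "total target sample size of 2,400 individuals". Table 2 is not updated.

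**The concern.** A detectable effect has a meaning only together with a power. A reader told that a trial should detect a 39% reduction will usually take this to mean that it has a good chance, by convention 80% or more, of a significant result if the true reduction is 39%. If the figure is really the smallest observed difference that would be significant, the chance is much lower.

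Three of the six primary outcomes are affected, and Table 2 is the article's only numerical guide to what the trial can detect using its own baseline data. A reader of a non-significant result could wrongly conclude that a reduction of the tabulated size had been reliably ruled out.

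**Working it through.** **Inputs.** There are four sites per arm and an unpaired t-test (Primary analysis), so 4 + 4 − 2 = 6 df and t(0.975) = 2.447. Prevalence p0, cluster size m and k_m come from Table 2. For physical IPV the table prints k_m as <0.1, and the text's assumed value of 0.1 is used.

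**Formula.** SE = √{[p0(1−p0)/m + p1(1−p1)/m + k²(p0² + p1²)]/4}, and 95% CI = difference ± 2.447 × SE.

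**Table 1 first.** For 30% v 22.5%, m = 75 and k = 0.1, SE = 4.04 points and the interval is 7.5 ± 9.9, or −2.4 to 17.4, as printed. The same formula reproduces all 48 Table 1 intervals to within 0.1 point. With z = 1.96 the interval would be −0.4 to 15.4, which does not match.

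**Table 2 as a significance threshold.** The relative reductions are 9/23 = 39%, 7/12 = 58% and 15/45 = 33%. The just-significant difference solves d = 2.447 × SE(d), with p1 = p0 − d.

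| Outcome | p0, m, k | Just-significant d | Printed | SE at printed d | 95% CI if printed d is observed |
|---|---|---|---|---|---|
| Physical IPV | 23%, 72, 0.10 | 8.6 | 9 | 3.48 | 0.5 to 17.5 |
| Sexual IPV | 12%, 72, 0.16 | 6.3 | 7 | 2.53 | 0.8 to 13.2 |
| Concurrency | 45%, 83, 0.17 | 14.5 | 15 | 5.91 | 0.5 to 29.5 |

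Rounding up gives all three printed values. For physical IPV, SE = √{[0.00246 + 0.00167 + 0.00073]/4} = 0.0348.

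**Does an 80% power formula give 9, 7 and 15?** The normal-theory form, d = 2.80 × SE, gives 9.7, 7.1 and 16.4. The Hayes–Bennett form with one extra cluster per arm gives 11.0, 8.0 and 18.6; with two extra, 13.0, 9.3 and 22.1. None fits all three rows.

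**Power at the printed differences.** This is the chance that a noncentral t on 6 df, with noncentrality d/SE, exceeds 2.447.

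- Physical IPV: 9/3.48 = 2.58, power 58%.
- Sexual IPV: 7/2.53 = 2.77, power 64%.
- Concurrency: 15/5.91 = 2.54, power 57%.

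Simulating the planned t-test on log prevalences gives 56%, 61% and 56%.

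**80% power at the printed cluster sizes.** The noncentrality must be 3.37. Solving d = 3.37 × SE(d) gives 11.4 points (49%), 8.2 points (68%) and 19.2 points (43%).

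**Follow-up sample.** 2,400/8 = 300 per site on average, against 200 at baseline, so clusters are 1.5 times larger on average. The protocol says only that each site has one or two parishes, so two splits were tried:

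| Assumed split | Power at 9, 7, 15 points | 80%-power difference (points) | Relative reduction |
|---|---|---|---|
| Every cluster 1.5 times larger (m = 108, 108, about 124) | 72%, 77%, 63% | 9.8, 7.2, 18.1 | 43%, 60%, 40% |
| Two sites per arm doubled, two unchanged | 68%, 74%, 61% | 10.2, 7.5, 18.4 | 45%, 62%, 41% |

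**The case against.** **No target is contradicted.** The protocol states no power, and Table 1 is openly about precision. That is correct, and 80% is a convention used here as a yardstick. A reader might infer that the plan misses a power it promised; it promises none. What remains is that a table of detectable effects and a claim to be able to detect them do not have a definite meaning without a power. A fuller protocol might supply one, but the published sentence would still mislead as worded.

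**The missing power term is inferred.** This also stands. The sexual IPV threshold of 6.3 would ordinarily round to 6, while a normal-theory 80% calculation gives 7.1. That calculation also gives 9.0 for physical IPV if k = 0. It fails for concurrency (16.4 against 15), and the text says 0.1 was assumed for physical IPV. The threshold reading is therefore the best fit, not a certainty. The power figures do not depend on how the printed values were derived.

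**The follow-up survey is larger.** This is true and partly offsets the problem. A reader might take 57–64% as the power of the planned trial, but it describes Table 2 as printed. For sexual IPV the gap nearly closes (7 against 7.2 points with clusters 1.5 times larger). For physical IPV, k = 0 combined with that growth would give 81%, so the shortfall there depends on the protocol's own k_m of 0.1.

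**The limits are admitted elsewhere.** The section on coherence and plausibility and the Discussion concede limited power and low precision, and effects will be reported with confidence intervals. This reduces the harm. Neither place says that the Table 2 effects have only moderate power.

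**Conclusion.** The point holds as one of labelling and overstated ability to detect. The printed reductions of 39%, 58% and 33% have no stated power and best match just-significant observed differences. At Table 2's own inputs, power for true effects of that size is about 58%, 64% and 57%. With clusters 1.5 times larger at follow-up it is about 72%, 77% and 63%.

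The results rest on the 6-df unpaired test, Table 2's prevalences and k_m (0.1 for physical IPV), and an assumed distribution of the larger sample across sites. They also carry a within-pair k_m into an unpaired analysis, as Table 2 used with this test implies. If variation between sites within an arm is larger than that, power is lower.

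Two stronger readings are not supported. One is that the trial has only an even chance of detecting the printed effects: power of about 54% belongs to the unrounded thresholds of 8.6, 6.3 and 14.5 points. The other is that a single set of corrected follow-up reductions can be stated: the protocol does not give the split by site, so only a range is available. Nothing here bears on the validity of the design or the planned analysis.

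**What to change.** Do one of two things.

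1. **Relabel.** Retitle the two Table 2 columns as the smallest observed difference, and relative reduction, that would reach p<0.05. Note that power is about 57–64% for true effects of the printed size at baseline cluster sizes. Delete the statements that the trial should be able to detect these reductions.
2. **Recompute.** Give Table 2 at a stated power, using the 6-df test and the actual follow-up cluster sizes, and put the power in the title. At 80% the reductions are about 49%, 68% and 43% at the printed cluster sizes. At follow-up they are roughly 43–45%, 60–62% and 40–41%, depending on the assumed split, so the final figures should come from the actual site sizes.

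The cost is restated, less favourable figures only. Design, data collection and analysis do not change.
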